4. MMSE>21	
5. Moderate to severe upper limb motor impairment, defined as a baseline Fugl-Meyer Assessment for the Upper Extremity (FMA-UE) score between 0 and 40	

Complete assessments will be performed at T0, T1, and T2 for both groups (Figure 2 and Table 2).

**Figure 2 fig2:**
[figure not shown]
Assessments and interventions.

**Table 2 tab2:** Schedule of assessments and outcome measures.

Domain	Outcome measure	Specific variables	Timepoint
Primary	FMA-UE	Total score (0–66)	T0, T1, T2
Secondary	fNIRS	HbO/HbR concentration, Laterality Index (LI)	T0, T1, T2
	TMS-MEP	RMT, MEP Amplitude, MEP Latency, Interhemispheric Ratio	T0, T1, T2
Other	Demographics and clinical data	Age, sex, stroke type, lesion location, time since stroke, etc.	T0

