### Participants

#### Sample size

Based on an F-test (ANOVA) with the following parameters: a conservative effect size [*f* = 0.4, based on a meta-analysis of tDCS studies for post-stroke UE recovery (13)], *α* error probability = 0.05, power (1-*β*) = 0.95, numerator df = 1, number of groups = 2, the total sample size is calculated in G-power. Accounting for an anticipated 20% attrition rate, the final required sample size is 70 participants, with 35 in each of the two groups.

**Experimental group:** Patients who receive active tDCS for 10 consecutive days with 20 min each day.**Control group:** Patients who receive sham tDCS.

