#### Randomization and blinding

This study will adhere to the CONSORT guidelines for randomized controlled trials (14). A computer-generated block randomization sequence (with varying block sizes) will be created by an independent statistician not involved in participant recruitment or assessment. The allocation sequence will be concealed in sequentially numbered, opaque, sealed envelopes. After obtaining baseline assessments (T0), a research assistant not involved in the study will open the next envelope to assign the participant to either the active or sham group.

This is a double-blind trial. Participants, the outcome assessors (who perform the FMA-UE, fNIRS, and TMS assessments), and the occupational therapists delivering the conventional rehabilitation will be blinded to group assignment. The investigator responsible for setting up and initiating the tDCS device will not be blinded, as they must input the correct stimulation code (active/sham) for the device. However, this investigator will have no role in outcome assessment or data analysis.

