### Statistical analysis

The primary analysis will follow the Intention-to-Treat (ITT) principle, including all randomized participants in the groups to which they were originally assigned. For the primary outcome (FMA-UE), missing data will be handled using multiple imputation. A per-protocol (PP) analysis will also be conducted as a sensitivity analysis. To test the primary hypothesis, a mixed-model Analysis of Variance (ANOVA) with factors for Group (active, sham) and Time (T0, T1, T2) will be used to test for the crucial Group x Time interaction effect.

Descriptive statistics will be employed to characterize participants’ clinical profiles. Between-group comparisons will be performed using chi-square tests for categorical variables and independent samples t-tests for continuous variables. Prior to parametric testing, data normality and variance homogeneity will be assessed using the Kolmogorov–Smirnov test and Levene test in the SPSS. All statistical analyses will be performed using SPSS software (version 20.0; SPSS Inc., Chicago, IL, USA). A *p*-value <0.05 will be considered as statistically significant. In addition to the primary analysis, exploratory subgroup analyses will be conducted based on baseline impairment severity (FMA-UE score: moderate [20–40] vs. severe [0–19]) to investigate potential differential treatment effects.

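### The primary FMA-UE model contains only Group and Time and ignores ipsilesional MEP status, available from T0 TMS before allocation; if that status predicts FMA-UE change, precision is lost

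*Protocol article*

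**What the plan says.** All references are to the protocol article.

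- **Table 2** lists TMS-MEP as a secondary outcome at T0, T1 and T2, with the variables "RMT, MEP Amplitude, MEP Latency, Interhemispheric Ratio". The section on TMS-MEP measurement has MEPs recorded from M1 on both sides. It defines the resting motor threshold only through MEPs that are evoked, and gives no rule for a patient in whom none can be evoked.
- **Randomization and blinding** sets the order of events: "After obtaining baseline assessments (T0), a research assistant not involved in the study will open the next envelope". Randomisation is in blocks of varying size, and no stratification factor is stated.
- **Table 1** requires moderate to severe impairment, "defined as a baseline Fugl-Meyer Assessment for the Upper Extremity (FMA-UE) score between 0 and 40".
- **Statistical analysis** fixes the primary model: "a mixed-model Analysis of Variance (ANOVA) with factors for Group (active, sham) and Time (T0, T1, T2) will be used". The test of interest is the Group x Time interaction. T0 FMA-UE enters as one level of Time, and no covariate is named. Apart from that, baseline data bear on the primary outcome only through an exploratory subgroup analysis by FMA-UE severity.

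**The concern.** By the time the envelope is opened, the trial has stimulated the ipsilesional motor cortex of each patient who completes T0. Whether a response could be elicited is thus a pre-randomisation value that can safely be adjusted for, and one the trial already pays to collect. The stated primary model leaves it out, and so does the randomisation.

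The protocol regards corticospinal excitability as part of the mechanism of upper-limb recovery, so it is reasonable to suspect that patients with and without an ipsilesional MEP gain different amounts on the FMA-UE. If they do, two things follow:

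- The difference in gain sits in the error term of the Group x Time test and costs power.
- If one arm happens to receive more patients with an MEP, the treatment estimate moves in that arm's favour, and nothing in the model removes the shift.

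The Statistical analysis section names the primary model itself, so this is a stated choice and not merely a detail left to a later plan.

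**Working it through.** **The plan's own figure.** The Sample size section gives f = 0.4 ("based on a meta-analysis of tDCS studies for post-stroke UE recovery (13"), alpha ("error probability = 0.05"), and power, degrees of freedom and groups ("0.95, numerator df = 1, number of groups = 2"). With a noncentral F (lambda = f² x N; df 1 and N - 2), these inputs need N = 84 before attrition (power 95.2%), and 84 / 0.8 = 105 after it. The protocol states: "Accounting for an anticipated 20% attrition rate, the final required sample size is 70 participants, with 35 in each of the two groups". So 70 is not reproduced, and the abstract gives 48. That discrepancy is a separate matter. Here I take 70 less 20% = 56 completers, and also show 48 and 70.

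**Inputs not in the documents (assumptions).** Share without an ipsilesional MEP (p): 0.3-0.5. Difference in FMA-UE gain between the two kinds of patient (D): 3-8 points. Residual SD of change (sigma): 6-8.

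**Share of variance explained.** Partial R² = p(1-p)D² / [p(1-p)D² + sigma²].
- Low end: 0.21 x 9 / (0.21 x 9 + 64) = 1.89 / 65.89 = 0.029.
- High end: 0.25 x 64 / (0.25 x 64 + 36) = 16 / 52 = 0.308.
- Equivalent extra completers at 56, from 56 x R² / (1 - R²): 1.7 to 24.9.

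**Power at f = 0.4.** Unadjusted: df N - 2. Adjusted: f / sqrt(1 - R²) with df N - 3. This is a single-df comparison of change.

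| N | Unadjusted | R² = 0 | 0.05 | 0.10 | 0.20 | 0.30 |
|---|---|---|---|---|---|---|
| 48 | 77.4% | 77.4% | 79.5% | 81.6% | 85.8% | 90.0% |
| 56 | 83.6% | 83.6% | 85.4% | 87.2% | 90.7% | 94.0% |
| 70 | 91.0% | 91.0% | 92.3% | 93.5% | 95.8% | 97.6% |

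**Simulation of the Group x Time contrast (T0 against T1; 4,000 replicates).** Assumed: residual SD of change 5, treatment effect 4.25 points, half the patients with an MEP, and a 10-point difference in FMA-UE level between the two kinds of patient.

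| Extra gain if MEP present | N = 48, without / with MEP x Time | N = 70, without / with MEP x Time |
|---|---|---|
| 0 (level difference only) | 81.8 / 81.1% | 94.5 / 94.3% |
| 3 points | 78.5 / 81.3% | 92.0 / 93.7% |
| 5 points | 74.0 / 80.4% | 88.3 / 93.9% |
| 7 points | 66.0 / 81.2% | 82.4 / 93.8% |

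With no treatment effect, the unadjusted test rejects in 4.4-5.7% of replicates. A difference in level alone yields no gain, because Group x Time already removes it within patients.

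**Chance imbalance.** At 28 per arm, the SD of the difference in MEP share is sqrt(2p(1-p)/28) = 0.122-0.134, so the 95% half-width is 0.240-0.262. Multiplied by D, the shift is 3 x 0.240 = 0.72 to 8 x 0.262 = 2.10 points, against a minimal important difference that starts at 4.25 (Primary outcomes). With a prevalence of 30-50%, an imbalance of at least 20 percentage points has probability 15.5-19.3% at N = 48 and 8.9-12.0% at N = 70. With a 5-point difference in gain, a 20-point imbalance moves the estimate by 0.20 x 5 = 1.0 point.

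**The case against.** The strongest reply is that nothing in the protocol is wrong here. An unadjusted randomised comparison is valid, and choosing covariates is partly a matter of preference. Time since stroke and lesion location are also recorded at T0 and could be proposed in the same way. The following parts of the reply stand.

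- **Prognostic value is not established.** A reader might infer that the protocol's own reasoning makes MEP status a predictor of recovery. It does not say so. Hypothesis 3 concerns the effect of stimulation on MEPs, and the Secondary outcomes section presents TMS as a way to explain mechanism. Nor does Table 1 say that the entry range yields both kinds of patient. Loss of precision is therefore conditional, and at R² = 0 nothing is lost.
- **Validity is not at stake.** A reader might infer that uncorrected imbalance biases the test. Type I error stays near 5%, and the standard error covers random imbalance on average. Only the estimate conditional on the imbalance that occurs is affected, and only through differences in gain.
- **A main effect would not help.** Adding MEP status as a between-patient term leaves the Group x Time test unchanged.
- **The variable must be derived.** Table 2 lists no present/absent item and the TMS section has no rule for absence. Having the value for everyone also assumes that T0 TMS is completed in everyone.

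The core survives: the primary model is written down, the measurement precedes allocation, and adjusting for it costs very little even if it turns out not to be prognostic (under 1 power point in the simulation). The existence of other candidate covariates is no reason to leave this one unused.

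**Conclusion.** The point holds as a conditional one about efficiency. The stated primary model makes no use of a pre-randomisation value that T0 TMS can supply. If ipsilesional MEP status predicts FMA-UE change, the Group x Time test has less power than it could have, and chance imbalance in expected gain remains in the estimate.

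At f = 0.4 and 56 completers the gain from adjustment runs from nothing (R² = 0) through about 2 power points (0.05) to about 10 (0.30). The size rests on assumed prevalence, difference in gain and residual SD, none of which the documents give. The power table treats the comparison as a single-df test of change, and the simulation uses T0 and T1 only, so neither is an exact power figure for the three-time-point interaction.

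The documents do not support the stronger readings that precision is certainly lost or that the planned test is invalid. The change is worth making while it can still be prespecified, because adjustment chosen after the results are seen would be less credible.

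**What to change.** - In the TMS-MEP measurement section, add a one-line rule for when an ipsilesional MEP counts as not elicitable, so that each patient with a T0 TMS session is classified before the envelope is opened.
- In the Statistical analysis section, prespecify T0 ipsilesional MEP status (elicitable / not elicitable) in one of two ways: crossed with Time in the mixed ANOVA, or as a covariate in an ANCOVA of T1 and T2 FMA-UE adjusted for T0 FMA-UE.
- Include the same variable in the multiple imputation model, and tabulate it by arm with the baseline characteristics.

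The ANCOVA covariate costs one degree of freedom, and MEP x Time over three time points costs two. Otherwise the change needs only the added text, with no new data, visits or patients.

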#### fNIRS data acquisition and analysis

The fNIRS data is collected at 3 time points: pre-intervention (T0), post-intervention (T1), and one-month follow-up (T2). Participants will be asked to sit comfortably on chairs in a quiet room, avoiding external interference and instructed to keep still and relax during data collecting period. and relax. The first collection session is conducted before intervention. The fNIRS is continuously running before, during and after tDCS for 40 min in total (Figure 3). The fNIRS sessions at T1 and T2 is recorded in a resting state for 20 min without c-tDCS.

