#### Experimental procedure

Eligible participants with unilateral upper extremity motor impairment will be formally screened by a qualified rehabilitation physician according to the predefined inclusion/exclusion criteria (Table 1). Participants will be assigned randomly to the active or sham tDCS group after written informed consent is obtained. The detailed experimental workflow is outlined in Figure 1.

**Table 1 tab1:** Inclusion and exclusion criteria.

Inclusion criteria	Exclusion criteria
1. Diagnosis of a first-ever, unilateral, supratentorial ischemic or hemorrhagic stroke, confirmed by CT or MRI;	1. Current pregnancy, lactation or gestation
2. Post-stroke chronicity ranging from 1 week to 2 years;	2. Concurrent participation in clinical trials within the preceding 3 months
3. Ability to maintain assisted sitting posture for ≥40 min without distress;	3. Any clinically significant condition or circumstance deemed by the Principal Investigator to compromise participant safety or protocol adherence at any study phase.

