**Figure 3 fig3:**
[figure not shown]
Combined c-tDCS and fNIRS recording at T0. **(A)** depicts the location of anode. **(B)** shows the settings for c-tDCS and fNIRS recording.

The fNIRS data will be acquired using the NirSmart system (Danyang Huichuang Medical Equipment Co., Ltd., Jiangsu, China). This system continuously monitored concentration changes of oxygenated hemoglobin (HbO) and deoxygenated hemoglobin (HbR) in the cerebral cortex. The apparatus comprised dual-wavelength near-infrared light sources (730 nm and 850 nm light-emitting diodes, LEDs) and avalanche photodiodes (APDs) as detection elements. A configuration of 12 source optodes and 10 detector optodes generated 24 measurement channels. Source-detector separation averaged 3.0 cm (range: 2.7–3.3 cm) across all channels, with hemodynamic data sampled at 11 Hz (Figure 4). Channel coordinates and corresponding brain region calibrations are detailed in Supplementary Table 1.

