#### Interventions

In this study, conventional rehabilitation training is combined either with active tDCS in experimental group or sham tDCS in the control group. The experimental group receive c-tDCS for 10 days, with 20 min per day, while the control group receive pseudo-stimulation of the same duration. The ipsilesional cerebellar hemisphere is stimulated by the anodal tDCS with current intensity of 2 mA. The anode is placed vertically 3 cm lateral to the middle line at the inion level. The ipsilesional cerebellar hemisphere is stimulated by the anodal tDCS with a current intensity of 2 mA. The anode (5 cm×7 cm) is placed vertically 3 cm lateral to the inion. The cathode (5 cm ×7 cm) will be placed over the ipsilateral upper trapezius. In the control group, there is a gradual increase and decrease process of the current at the beginning and end, imitating the scalp discomfort when the current is initiated to ensure the accuracy of the blinding method.

The CULR of the paretic upper extremity includes electrical neuromuscular stimulation, active or passive range of motion training, and muscle strength training. Each CULR session will last for 45 min, delivered by a professional occupational therapist immediately after each tDCS session. The session will be structured as follows: ~15 min of neuromuscular electrical stimulation and passive/active-assisted range of motion exercises for the shoulder, elbow, wrist, and fingers; ~20 min of task-oriented training (e.g., reaching, grasping, manipulating objects of different sizes and weights); and ~10 min of muscle strengthening exercises using resistance bands or light weights. Both groups will receive the same standardized CULR procedure.

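### The T0 fNIRS recording includes a c-tDCS session, which conflicts with opening the envelope only after T0, and no pre-stimulation window is named as the fNIRS baseline

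*Protocol article*

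**What the plan says.** All references are to the protocol article.

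- **Allocation order** (*Randomization and blinding*): "After obtaining baseline assessments (T0), a research assistant not involved in the study will open the next envelope". The same section says the unblinded investigator must enter a code that makes the device deliver active or sham current.
- **What T0 contains** (*Experimental procedure*, Table 2): complete assessments at T0, T1 and T2, with fNIRS (HbO/HbR and laterality index, LI) listed at all three.
- **What the T0 fNIRS session is** (*fNIRS data acquisition and analysis*): T0 is labelled pre-intervention, and "The first collection session is conducted before intervention". The next sentence reads "The fNIRS is continuously running before, during and after tDCS for 40 min in total". The Figure 3 caption repeats the placement: "Combined c-tDCS and fNIRS recording at T0".
- **The later sessions** (same section): "The fNIRS sessions at T1 and T2 is recorded in a resting state for 20 min without c-tDCS".
- **Session length** (*Interventions*): "The experimental group receive c-tDCS for 10 days, with 20 min per day, while the control group receive pseudo-stimulation of the same duration".
- **How LI is formed** (*Secondary outcomes*): from wavelet amplitude of HbO in the 0.01–0.08 Hz band, before and after the intervention, with the same computation. No part of the T0 recording is named as its source.

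**The concern.** Two things do not fit.

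First, the order of events. A T0 assessment that includes stimulation cannot both finish before the envelope is opened and deliver the stimulation that the envelope assigns. Site staff following the text would have to break one instruction or the other.

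Second, the baseline. T0 and the later visits differ in condition (a recording that spans stimulation against rest alone) and in length (40 min against 20 min). Hypothesis 2 predicts a shift in the laterality index, so a change from T0 is what the fNIRS outcome is meant to show. If the baseline index includes minutes recorded under or after assigned stimulation, it is partly a post-treatment value. A baseline cannot be re-recorded once a participant has been stimulated, so the window needs to be fixed before enrolment.

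**Working it through.** The plan gives no figure to reproduce. The check is a comparison of statements plus arithmetic on minutes.

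**Step 1: which stimulation is given at T0?** The text does not say. There are two readings.

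| Reading | Envelope after T0? | Is T0 pre-stimulation? | Other conflict |
|---|---|---|---|
| (a) T0 stimulation follows the assigned arm | No: the device code must be known while T0 is still running | Only its first segment | Later part of T0 differs by arm |
| (b) Everyone receives the same stimulation before allocation | Possible | Only its first segment | If that stimulation is active, controls receive active current, although *Sample size* defines them as receiving sham |

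Reading (a) is the more natural, because the device has to be told which arm to deliver. Under neither reading is the whole T0 recording pre-intervention. Nor does the article say whether the T0 session is one of the 10.

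**Step 2: how much of T0 is unstimulated?** Inputs: T0 recording 40 min and T1/T2 recordings 20 min (*fNIRS data acquisition and analysis*); one session 20 min (*Interventions*). Assumption: the T0 session has that 20 min length.

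- Minutes outside stimulation: 40 − 20 = 20 = before + after.
- Share during or after stimulation = (40 − before)/40. Since before cannot exceed 20, the share is at least 20/40 = 50%.
- The recording continues after stimulation, so after > 0 and before < 20 min. The clean T0 rest is therefore shorter than the T1/T2 recordings under any split.

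The split is not given. Assumed values show the range:

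| Before / after (min) | During or after, share of 40 min | Clean rest relative to 20 min at T1/T2 |
|---|---|---|
| 5 / 15 | 35/40 = 87.5% | 5/20 = 25% |
| 10 / 10 | 30/40 = 75% | 10/20 = 50% |
| 15 / 5 | 25/40 = 62.5% | 15/20 = 75% |

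**Step 3: why length matters for this index.** At the lower band edge of 0.01 Hz, a window of m minutes holds 0.01 × 60 × m cycles. Ten minutes hold 6 cycles and 20 min hold 12. Unequal windows therefore estimate the slowest part of the band with unequal precision.

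**Step 4: what a whole-recording baseline would do.** Under (a), the active arm's T0 index would carry some acute effect of active current and the sham arm's would not, so T1−T0 and T2−T0 would differ between arms partly because of T0. If the acute effect has the same sign as the lasting one, the between-arm contrast shrinks; if the opposite, it grows. Under (b), randomization would balance the T0 index in expectation, but each change score would still compare a recording spanning stimulation with one at rest.

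**The case against.** The best defence is that the authors plainly intend separate phases. The abstract distinguishes resting-state from stimulation-induced responses. The Introduction and *Strength and limitations* treat the periods around stimulation as distinct. Preprocessing discards irrelevant intervals, and LI is to be computed the same way before and after the intervention. The natural inference is that the pre-stimulation rest is the baseline. The exact window is the kind of detail an article leaves to the full protocol, and the figures, which are not visible here, may show the timing.

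Much of this stands. Nowhere is LI said to be averaged over the 40 min, so a whole-recording baseline is a possibility left open, not a stated plan. A clean segment exists and can be recovered. But the order conflict is not an omission: the article states both halves of it, and the visible Figure 3 caption places c-tDCS at T0. The mismatch in condition and length between T0 and the later visits is also stated.

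A reader might go further than the document allows:

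- **That the primary outcome's baseline is contaminated.** Not supported. A baseline FMA-UE of 0 to 40 is an inclusion criterion, so a score must exist before enrolment. Nothing places FMA-UE or TMS after stimulation.
- **That allocation concealment is weakened.** Not shown. Concealment concerns whether recruiters can foresee the next assignment. The sequence comes from an independent statistician, with varying block sizes and sealed opaque envelopes. Opening an envelope part-way through T0, after consent and screening, discloses nothing in advance.
- **That *Experimental procedure* is a further contradiction.** It says "Participants will be assigned randomly to the active or sham tDCS group after written informed consent is obtained". Assignment after T0 is also after consent, so the two statements are compatible.
- **That 75% of the acute effect is absorbed and the result is biased towards no difference.** The 75% is a share of minutes under an assumed even split. LI is a ratio of wavelet amplitudes, not a linear average over time, and the direction depends on signs the document does not give.

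**Conclusion.** The concern holds for the allocation order and for the secondary fNIRS outcome (hypothesis 2).

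- The statements that the envelope follows T0 and that T0 fNIRS spans c-tDCS cannot both be followed if the T0 stimulation is the assigned one. If it is the same for all, the order can be kept but the pre-intervention label is still wrong.
- Given a 20 min session, at least half of the 40 min T0 recording is during or after stimulation, and the clean rest is shorter than the T1/T2 recordings. Neither statement depends on how the remaining 20 min are split.
- No text confines baseline HbO/HbR and LI to the clean rest. Distortion of change from T0 is conditional on using more than that rest. Its size and direction cannot be derived from the document.

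The primary analysis of FMA-UE, the TMS measures and allocation concealment are not shown to be affected.

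**What to change.** 1. Complete FMA-UE, TMS-MEP and a resting fNIRS segment before the envelope is opened, and call that T0.
2. Compute baseline HbO/HbR and LI only from this pre-stimulation rest, with the same window length at T0, T1 and T2.
3. Treat the segments recorded during and after the first assigned session as a separate acute-response outcome, compared between arms and not used as baseline.
4. Reconcile *Randomization and blinding*, *fNIRS data acquisition and analysis*, the Figure 3 caption and *Secondary outcomes* on this order. State which stimulation the recorded session delivers and how it relates to the 10 sessions.

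The cost is revised wording and a fixed order of procedures on the first day. If the common window is shorter than 20 min, LI at T1 and T2 is slightly less precise. Making the T0 rest 20 min long would avoid that loss but lengthen the first visit.
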